### **7.3.3 Carers**

For all participants (irrespective of capacity status) enrolled in the intervention arm of the medium- or high- risk subgroups, their carer will be invited to join the intervention arm, if their carer is willing and able to provide consent.

A member of the direct care team will approach their carer in person or over the phone to tell them about the study and decide whether the carer has capacity to give informed consent. If so, the clinician will determine their interest in taking part in the trial and gain consent to share their contact details with a member of the research team. Screening, eligibility, approach, and consent to contact will be documented in the CRF. A member of the research team will subsequently provide an explanation of the aims, methods, benefits and potential harms and a carer information leaflet. Carers will be given at least 24 hours to consider their participation in the study. A member of the research team will subsequently answer any questions prior to obtaining written informed consent to enter the trial. The number of carers

who declined (and why) will be documented. Should a carer decline to take part, this will not affect the patient participant enrolled in the study.

### **7.3.4 Therapists**

Therapists who were involved in delivery of the Stratify intervention arm of the feasibility trial will be invited to complete semi-structured interviews focused on treatment acceptability and fidelity (inclusive of barriers and facilitators to implementation). A member of the research team will outline the aims, methods, benefits and potential harms of the qualitative study and provide a participation information leaflet during therapist training prior to the start of the study. During this training sessions, therapists will be asked to provide consent to contact from the research team at the end of the study (their name and email address will be stored on an Excel Spreadsheet on secure KCL SharePoint server). At the end of the study a member of the research team will contact those who provided consent to contact and answer any questions prior to obtaining written informed consent to the interview study.

## **7.4 Randomisation procedures**

The randomisation approach was designed with a statistician (SA) and validated for use prior to implementation. Once a participant has provided informed consent, they will be allocated a participant identification number (PID). Baseline data will subsequently be collected by the research team prior to randomisation. Randomisation will follow a 1:1 random allocation sequence stratified by subgroup assignment (low-, medium-, high- risk), using a secure internet-based system, developed and maintained by King's Clinical Trials Unit to ensure allocation concealment. Treatment allocation will be revealed (after randomisation) to a member of the research team, linked to the participant number, and the clinical team will be notified.

## **7.5 Blinding**

The group allocator, assessor of adverse and serious adverse events, assessor of patient reported outcomes, and statistical analyst will be blind to group allocation.

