| Ethnicity                                | Categorical            | Patient interview     | Site therapist |                           | X               |               |                            |                  |                   |
| Fracture type                            | Categorical            | Patient notes         | Site therapist |                           | X               |               |                            |                  |                   |
| Surgery type                             | Categorical            | Patient notes         | Site therapist |                           | X               |               |                            |                  |                   |
| Abbreviated Mental Test                  | Numerical              | Patient notes         | Site therapist |                           | X               |               |                            |                  |                   |
| Mini Nutritional Assessment              | Numerical              | Patient notes         | Site therapist |                           | X               |               |                            |                  |                   |
| Hospital concerns about falls assessment | Numerical              | Patient interview     | Research team  |                           | X               |               |                            |                  |                   |
| Residence                                | Categorical            | Patient interview     | Site therapist |                           | X (prefracture) |               |                            | X                | X                 |
| Living status                            | Categorical            | Patient interview     | Site therapist |                           | X (prefracture) |               |                            | X                | X                 |
| Mobility                                 | Categorical            | Patient interview     | Site therapist |                           | X (prefracture) |               |                            |                  | X                 |
| EuroQoL EQ-5D-5L                         | Numerical              | Patient questionnaire | Research team  |                           | X               |               |                            | X                | X                 |

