## **7.6 Schedule of assessments for each visit**

Participants will undergo screening, baseline assessment, assessment at intervention end, and assessment at 12-weeks post-randomisation. Assessments at baseline and intervention end will be in-person, over the telephone, or via MS TEAMS (the mode will be documented). Assessments at 12-weeks post-randomisation will be completed over the telephone or via MS TEAMS.

Screening for eligibility: Confirmation planned surgical intervention for hip fracture and aged 60 years or more. Additional assessment prior to consent will include a member of the direct care team's determination of capacity, confirmation whether the potential participant is enrolled in any other study, and subgroup assignment (to ensure no more than 12 participants from one subgroup enrolled to each arm of the study).

Baseline: Following consent and prior to randomisation, a member of the research team will collect the following participant characteristics: age, sex, ethnicity, fracture type, surgery type, Abbreviated Mental Test, Mini Nutritional Assessment, hospital concerns about falls

assessment, pre-fracture residential status (home, residential home, nursing home), living status (lives alone, with independent spouse, with dependent spouse, with family, with other), prefracture mobility. They will also collect patient-reported outcome measures which satisfy the core outcome set for hip fracture trials:

- a) health-related quality of life (EuroQoL EQ-5D-5L)
- b) activities of daily living (Barthel Index; Nottingham Extended Activities of Daily Living)
- c) falls related self-efficacy (Short Falls Efficacy Scale-International)
- d) pain (Numeric Rating Scale)
- e) walking ability (New Mobility Score)

A bespoke resource use data collection form will also be collected. This form can be collected both prior to and/or after randomisation but will be completed prior to discharge (and intervention end).

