|                 | Walk indoors accompanied by another person and using two crutches while completing a series of cognitive tasks e.g., reciting every other letter of the alphabet, counting to 100 in increments of 5. |

2. Up to five mobility training sessions with progressions (See Box 3 for example of progressions).

Box 3: Example of progressions towards behaviour goal

|                                                                                                                     |                                                                                                                    |
|---------------------------------------------------------------------------------------------------------------------|--------------------------------------------------------------------------------------------------------------------|
| Behaviour goal                                                                                                      | Walk continuously indoors on flat ground for 3 minutes with the use of two crutches independently.                 |
| Progressions
towards goal
[figure not shown] | Walk continuously indoors on flat ground for 3 minutes with the use of two crutches accompanied by another person. |
|                                                                                                                     | Walk continuously indoors on flat ground for 3 minutes with the use of two crutches accompanied by another person. |
|                                                                                                                     | Walk continuously indoors on flat ground for 3 minutes with the use of a frame independently.                      |
|                                                                                                                     | Walk continuously indoors on flat ground for 3 minutes with the use of a frame accompanied by another person.      |

3. Progress chart template completed and placed at bedside indicating to the participant what they can complete independently and/or what they should be supported by team (including carer) to complete.
4. Carer (as available)

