### **7.9 Follow up procedures**

Participants and their carers (where applicable) will be followed-up by the research team via telephone/MS TEAMS at the end of the intervention and at 12-weeks post-randomisation to complete assessments and interviews. Therapists will be followed up by the research team by email at the end of the intervention to seek informed consent to participate in the qualitative study. Where consent is obtained, therapists will complete semi-structured interviews over the telephone/MS TEAMS with a member of the research team.

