Where AEs/SAEs occur, the team (direct care team delivering the intervention and control arms) will follow Good Clinical Practice Guidelines for the reporting to the medical team responsible for the participant's care and notify the Principal Investigator (PI). PIs at all sites will report all AEs/SAEs to the CI via the study electronic database (REDCap). The CI will review all AEs/SAEs against GSTFTs guide for assessment of whether the event is related

to the intervention or not. The CI will then be responsible for reporting SAEs to the Sponsors R&D office.

All SAEs that are to be reported to the R&D office will be signed and dated and completed by the CI. Where a related and expected SAE occurs that does not require immediate reporting, this SAE will be reported in the Annual Progress Report and copied to the R&D office, alongside any AEs that occur that are not classified as 'serious'.

Related and unexpected SAEs will be reported immediately upon knowledge of the event to the R&D office and always within 24 hours. Reports of related and unexpected SAEs will be submitted to the Main NHS/ HSC REC within 15 days of the Chief Investigator becoming aware of the event, using the appropriate template. The form will be completed in typescript and signed by the Chief Investigator. The main REC will acknowledge receipt of safety reports within 30 days. A copy of the SAE notification and acknowledgement receipt will also be sent to the R&D office. The SAE will also be documented as unexpected and related in the CRF, participants medical notes if they are in hospital at the time, annual report (with site copied), and on Datix.

A joint Trial Steering and Data Monitoring Committee (TSDMC) will be informed of the number, nature and review outcomes for all serious adverse events and be asked to recommend any necessary actions.

Where an SAE occurs that does not require immediate reporting, this SAE will be reported in the Annual Progress Report and copied to the R&D office, alongside any AEs that occur that are not classified as 'serious'. The final report will detail the number (events and individuals) and nature of all events (AEs and SAEs) reported to members of each site and/or research team and will be submitted to the REC with the sponsor copied.

Please see Appendix 1 and 2 for further information on reporting of SAEs.

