### **11.3 *Protocol compliance***

A protocol deviation is defined as an unintended departure from the expected conduct of the study protocol, which does not need to be reported to the sponsor. The CI will monitor protocol deviations by monitoring treatment logs completed by treating therapists after each session against the treatment allocation. Any deviations noted will be listed in a deviation log. Significant deviations to the protocol or deviations which are found to frequently recur will be assessed by the CI to see if an amendment to the protocol is required. Any significant deviations to the protocol or recurring deviations will be reported to sponsor and action taken through Corrective and Preventative Actions.

A 'serious breach' is defined as a breach likely to effect to a significant degree:

- The safety or physical or mental integrity of the participants of the trial;
- The scientific value of the trial.

The CI and sponsor will be notified by the site PI immediately if a serious breach occurs. The breach will then be reported to the REC Committee with the sponsor in copy within 7 calendar days of the breach being confirmed as serious.

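### Section 7.5 calls the adverse-event assessor blind, but the only named assessor of relatedness also checks treatment logs against allocation; separately, Table 1 has the treating role record follow-up residence and living status

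*Protocol*

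**What the plan says.** Protocol section 7.5 lists who is blind: the group allocator and the "assessor of adverse and serious adverse events, assessor of patient reported outcomes, and statistical analyst will be blind to group allocation".

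**Adverse events.** Under section 10, events are reported by the "direct care team delivering the intervention and control arms", and then: "The CI will review all AEs/SAEs against GSTFTs guide for assessment of whether the event is related" to the intervention. Section 11.3 states: "The CI will monitor protocol deviations by monitoring treatment logs completed by treating therapists after each session against the treatment allocation". Section 13.2 describes the same comparison of logs with allocation but gives it to the research team.

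**Follow-up status items.** In Table 1 the person completing the residence, living status and mobility rows is the "Site therapist". Residence and living status are marked at baseline, intervention end and 12 weeks; mobility is marked at baseline and 12 weeks only. The same table gives delivery of the control and intervention treatments, and the treatment logs, to the site therapist. Section 7.6 has a research-team member collect 12-week residence and living status. Section 12.2 places both items, at intervention end and follow-up, in a database entered by research-team users who are blind.

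**Mode at intervention end.** Section 7.6 says: "Assessments at baseline and intervention end will be in-person, over the telephone, or via MS TEAMS (the mode will be documented"; section 12.1 agrees. Section 7.9 says participants "will be followed-up by the research team via telephone/MS TEAMS at the end of the intervention". For the medium-risk intervention, section 7.7.2 requires: "Progress chart template completed and placed at bedside indicating to the participant what they can complete independently". Section 7.7.3 has an equivalent chart for the high-risk intervention.

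**The concern.** A blinding statement is only as good as the task assignments behind it. Here the role that classifies events as related or unrelated is also told to read what each participant received against what was allocated. Section 10 notes that prolonged hospitalisation after a fall may be expected and related to the intervention, because the intervention encourages activity. The relatedness judgement is thus the kind that knowledge of allocation can sway, and together with expectedness it decides whether an event goes to the R&D office within 24 hours and to the ethics committee within 15 days.

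Residence and living status are obtained by interview and used to determine change to a higher level of care, which section 12.1 treats as a key performance indicator. If the treating role records them, the arms are compared on data collected with knowledge of treatment, while section 12.2 tells the reader that the users are blind.

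**Working it through.** No stated figure is in dispute. The check sets the role assignments side by side.

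**1. Adverse-event assessor**

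| Task | Role | Section |
|---|---|---|
| Identify and report events | Care team delivering both arms | 10 |
| Judge relatedness of all events | CI | 10 |
| Compare logs with allocation | CI | 11.3 |
| Compare logs with allocation | Research team | 13.2 |
| Assess events, stated blind | Not named | 7.5 |

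The second and third rows name the same role. Nobody else is named for relatedness, so under 11.3 as written every relatedness judgement is made by someone with access to allocation. Section 13.2 shows that the log check need not belong to the CI.

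**2. Follow-up status items**

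| Item | Table 1 | Section 7.6 | Section 12.2 |
|---|---|---|---|
| Residence and living status, intervention end | Site therapist | A member of the team (unspecified) | Blind research-team users |
| Residence and living status, 12 weeks | Site therapist | Research team | Blind research-team users |
| Mobility category, 12 weeks | Site therapist | Not listed | Not listed at follow-up |
| EQ-5D-5L, Barthel, Nottingham Extended ADL, Short FES-I, pain rating, New Mobility Score | Research team | Research team at 12 weeks | Blind research-team users |

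The first two rows cannot be reconciled with 12.2, and the second also contradicts 7.6. For mobility, Table 1 stands alone: there is no contradiction, but the treating role records it. The last row is consistent, so section 7.5 is not breached for patient-reported outcomes. Sections 12.2 and 12.3 give therapists entry and access to the database holding allocation and treatment logs, so the site-therapist role is not blind whichever individual fills it.

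**3. Mode at intervention end**

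Sections 7.6 and 12.1 allow in-person assessment; section 7.9 gives telephone or MS TEAMS. Charts are described only for the medium- and high-risk intervention groups. To see how many participants would have one:

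- Section 7.2 targets 20 per subgroup. With 1:1 allocation that is 20/2 = 10 per subgroup per arm, so 10 + 10 = 20 of 30 intervention participants.
- Section 7.6 caps each subgroup at 12 per arm. The fewest with a chart is 30 − 12 = 18; the most is 12 + 12 = 24.

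This counts charts, not unblindings. The number of assessments done in person, and how many of those take place beside the chart, is not given and cannot be derived.

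**The case against.** The strongest reply on adverse events is that the assessor in section 7.5 could be the team member who, under section 7.6, collects events alongside the questionnaires. On that reading 7.5 says nothing about the CI. But relatedness would then be judged unblinded without the protocol saying so, and a reader of 7.5 would assume otherwise. It is also fair that relatedness may be hard to judge without knowing what was delivered; that is a reason to offer withdrawal of the claim as an alternative.

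On Table 1, one completion cell serves all time points, and the same mismatch with section 7.6 affects baseline items such as age and fracture type. This may be a drafting slip. At baseline it does no harm to blinding, because collection precedes randomisation; at follow-up it does.

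A reader might infer more than the documents support:

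- *That therapists collect the questionnaires.* They do not; Table 1 gives those to the research team.
- *That about 20 of 30 intervention participants would be unblinded by bedside charts.* The text says in-person, not bedside. Section 7.9 points to remote contact, and the visit records length of stay and residence, which suggests contact around or after discharge. The documents also do not say whether usual care uses any bedside chart.
- *That the count of inadvertent unblinding (secondary objective 5) is invalidated.* Event review by the CI and therapist entries are not inadvertent unblinding of outcome assessors, and a chart seen in passing is just what that objective would count.

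Finally, this is a feasibility trial whose safety objective is a count of events, which relatedness does not change.

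**Conclusion.** Two inconsistencies are established. First, the blinding stated for adverse events in section 7.5 does not hold for relatedness under sections 10 and 11.3, and this covers every event. Second, Table 1 assigns follow-up residence and living status to an unblinded treating role, against sections 7.6 and 12.2, and it does the same for mobility at 12 weeks without a competing statement. The third matter, in-person assessment near a bedside chart, is a possible route to unblinding of unknown frequency, limited to intervention end because 12-week assessments are remote.

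The consequence is confined to relatedness classification and the between-arm picture for residence and living status. None of the progression criteria in section 14.4 (eligibility, recruitment, randomisation, fidelity, EQ-5D completeness) uses these. The conclusion assumes that the CI personally does what sections 10 and 11.3 assign, and that Table 1 is followed as printed.

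**What to change.** 1. **Sections 11.3 and 7.5.** Give the comparison of logs with allocation to an unblinded research-team member who does not review adverse events, in line with section 13.2; sections 7.4 and 12.2 already provide for research-team members who know allocation. Have the adverse-event reviewer record a first relatedness assessment without allocation. Reports come from the treating team, so they would need to omit the arm. If relatedness cannot sensibly be judged that way, withdraw the blinding claim for adverse events from 7.5.
2. **Table 1.** Change the completing role to the blinded research team for residence and living status at intervention end and 12 weeks, and for mobility at 12 weeks.
3. **Sections 7.6, 12.1 and 7.9.** State one rule for the mode of the intervention-end assessment. If in-person contact is kept, hold it away from the bed space.

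The cost is a small reassignment among existing staff, wording changes, and possibly less in-person contact at intervention end. No extra participants or analyses are needed.

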## **7.6 Schedule of assessments for each visit**

Participants will undergo screening, baseline assessment, assessment at intervention end, and assessment at 12-weeks post-randomisation. Assessments at baseline and intervention end will be in-person, over the telephone, or via MS TEAMS (the mode will be documented). Assessments at 12-weeks post-randomisation will be completed over the telephone or via MS TEAMS.

Screening for eligibility: Confirmation planned surgical intervention for hip fracture and aged 60 years or more. Additional assessment prior to consent will include a member of the direct care team's determination of capacity, confirmation whether the potential participant is enrolled in any other study, and subgroup assignment (to ensure no more than 12 participants from one subgroup enrolled to each arm of the study).

Baseline: Following consent and prior to randomisation, a member of the research team will collect the following participant characteristics: age, sex, ethnicity, fracture type, surgery type, Abbreviated Mental Test, Mini Nutritional Assessment, hospital concerns about falls

assessment, pre-fracture residential status (home, residential home, nursing home), living status (lives alone, with independent spouse, with dependent spouse, with family, with other), prefracture mobility. They will also collect patient-reported outcome measures which satisfy the core outcome set for hip fracture trials:

- a) health-related quality of life (EuroQoL EQ-5D-5L)
- b) activities of daily living (Barthel Index; Nottingham Extended Activities of Daily Living)
- c) falls related self-efficacy (Short Falls Efficacy Scale-International)
- d) pain (Numeric Rating Scale)
- e) walking ability (New Mobility Score)

A bespoke resource use data collection form will also be collected. This form can be collected both prior to and/or after randomisation but will be completed prior to discharge (and intervention end).

During the intervention: The research team will conduct fidelity observations of at least twelve therapist-led sessions (four assessments for each subgroup in the intervention arm) following verbal consent from the therapist and participant engaged in each session. The research team will conduct fidelity observations of at least four carer training sessions (two assessments for medium- and high- subgroup in the intervention arm). Participants in the intervention arm will be asked to complete a participant diary indicating the extent to which they practices training without healthcare professionals.

Intervention end: At the intervention end, a member of the team will collect data on hospital length of stay, mortality (death records will be checked online prior to contacting the participant/their carer), place of residence (home, residential home, nursing home), living status (lives alone, with independent spouse, with dependent spouse, with family, with other), adverse/serious adverse events, as well as the following patient-reported outcome measures:

- a) health-related quality of life (EuroQoL EQ-5D-5L)
- b) activities of daily living (Barthel Index; Nottingham Extended Activities of Daily Living)
- c) falls related self-efficacy (Short Falls Efficacy Scale-International)
- d) pain (Numeric Rating Scale)
- e) walking ability (New Mobility Score)

They will also purposively sample participants with different risk subgroup assignment (low, medium, high), for telephone/MS TEAMS semi-structured interviews focused on treatment acceptability and fidelity (inclusive of barriers and facilitators to implementation). Interviews will target 50% of intervention participants but continue until no new themes are identified.

At intervention end, purposively sampled therapists with different professional backgrounds (physiotherapist, occupational therapist, therapy assistant) and who were involved in the delivery of the Stratify intervention arm will be followed up by the research team by email to seek informed consent to participate in the qualitative study. Where consent is obtained, telephone/MS TEAMS semi-structured interviews focused on treatment acceptability and

fidelity (inclusive of barriers and facilitators to implementation) will be conducted. Interviews will target 100% of therapist involved in delivery of the intervention arm but continue until no new themes are identified.

**12-week follow-up:** At 12-week follow up, a member of the research team will collect data related to mortality (death records will be checked online prior to contacting the participant/their carer), readmissions (and admitting diagnosis), place of residence (home, residential home, nursing home), and living status (lives alone, with independent spouse, with dependent spouse, with family, with other), any adverse/serious adverse events, as well as the following patient-reported outcome measures:

- a) health-related quality of life (EuroQoL EQ-5D-5L)
- b) activities of daily living (Barthel Index; Nottingham Extended Activities of Daily Living)
- c) falls related self-efficacy (Short Falls Efficacy Scale-International)
- d) pain (Numeric Rating Scale)
- e) walking ability (New Mobility Score)
- f) bespoke resource use data collection form (including health and social care, informal care and paid/unpaid work)

Participants who are non-English language speakers will be supported to complete assessments (except patient reported outcome measures) with the use of language support at the Trust. Patient-reported outcome measures which have an established translated, validated, and (where applicable) culturally adapted version in the appropriate language will be circulated by post to the participant with a pre-paid envelope for return direct to the research team.

For carers recruited to the study, we will collect data relating to their age, sex, education, employment (not employed, part-time, full time), children (yes, no), and relationship to the participant. A member of the research team will purposively sample participants who are carers of those assigned to different risk subgroups (low, medium, high) for telephone/MS TEAMS semi-structured interviews focused on treatment acceptability and fidelity (inclusive of barriers and facilitators to implementation). Interviews will target 50% of intervention carers but continue until no new themes are identified.

